**Methods:**

A total of 70 participants are expected to be recruited in this single blind randomized controlled trial. Computer-generated random numbers will be used to randomize the participants into 3 groups, namely, the rebound exercise group, the circuit exercise group, and the control group. Measurements will be taken at baseline and at the end of the 8 weeks of the study. Participants’ musculoskeletal pain will be assessed using the visual analog scale, quality of life will be assessed using the SF 12 Health Survey Questionnaire, depression using the Beck Depression Inventory, respiratory parameters using the spirometer, and biochemical parameters such as glucose level and cholesterol level using the glucometer. Data will be analyzed using descriptive statistics and inferential statistics of multivariate analysis of variance between the groups and paired t test within the group. Alpha will be set at .05.

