
### Sample Size and Power Calculation

The sample size (N) will be determined using Cohen table [29] at alpha=.05 and degree of freedom (µ)=k−1, where k is the number of groups, with effect size f=0.35. From the previous study [17] and power (w) 80%, sample size n=20. Sample size (N) will be 60, and 12 extra participants will be added to make room for attrition. Therefore, the sample size will be 72 participants, and each group will be 24 participants.

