### Procedures

Assessment of participants will be conducted at 2 stages: at baseline and at the end of 8 weeks of intervention. To ensure a comprehensive assessment, a battery of measures was chosen covering the WHO-ICF model [30]. Certain tools were selected to cover the 3 key domains proposed by the ICF: body structures and function (hematological variables, MSKP, and respiratory parameters), activity, and participation (QoL and depression). At baseline, participants will be assessed for sociodemographic characteristics, which will include personal demographic information and diabetes-specific information. The personal demographic information will include age, sex, height, weight, marital status, educational qualification, and employment. The diabetes-specific information will include type of diabetes and duration since diagnosis. At the baseline, the outcome measures to be used for these assessments are presented in the measurement section. Table 1 shows the instruments.

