### Data Analysis

Preliminary analysis will be performed to test the normality of the data using the Kolmogorov V-Smirnov test before the analysis. Demographic data will be analyzed using descriptive statistics, whereas data on QoL and depression will be analyzed within the group using the Wilcoxon signed rank test and between the groups using the Kruskal-Wallis test. Post hoc test will be used for any significant F values.

The paired *t* test will be used within the group for pain scores, fasting glucose, and cholesterol level of the participants and between groups using 1-way multivariate analysis of variance. Post hoc test will be used for any significant F values. The level of significance will be set at .05. The SPSS version 23 will be used for the analysis.

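### The between-group MANOVA for pain, glucose and cholesterol has no baseline term and can tie the pain score to the blood values, and the only follow-up visit is worded inconsistently

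*Protocol article*

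**What the plan says.** **Size and loss.** Sample Size and Power Calculation states: "Sample size (N) will be 60, and 12 extra participants will be added to make room for attrition". It continues: "Therefore, the sample size will be 72 participants, and each group will be 24 participants".

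**Between-group test.** Data Analysis assigns the paired t test within groups to "pain scores, fasting glucose, and cholesterol level of the participants and between groups using 1-way multivariate analysis of variance". The Abstract also names MANOVA as the between-group method. Quality of life and depression are handled separately, by Wilcoxon signed rank within groups and Kruskal-Wallis between groups.

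**Follow-up visit.** There is one assessment after baseline. Procedures says: "Assessment of participants will be conducted at 2 stages: at baseline and at the end of 8 weeks of intervention". Under Measurement, the blood values are timed by weeks of the programme and the spirometry by weeks of the study. The Abstract also counts weeks of the study.

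**The concern.** Three features work together.

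- **No baseline term.** A 1-way MANOVA has arm as its only factor. Baseline values of pain, glucose and cholesterol are collected but, as the test is named, do not enter the arm comparison. That gives up precision. It also leaves the comparison exposed if the people lost differ at baseline between arms.
- **Coupled outcomes.** MANOVA uses only records complete on all its dependent variables unless missing values are imputed. If pain and the blood values form one model, a participant who attends without a usable blood sample also loses a pain score that was recorded.
- **Ambiguous visit.** If the visit belongs to the end of the intervention, a participant who stops exercising in week 3 arguably never reaches it. If it belongs to study time, that participant is due at week 8. Controls have no programme to stop, so the first reading could make follow-up unequal by arm. A later visit could not repair the comparison, because controls move into exercise after 8 weeks.

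Unequal loss is plausible: the exercise arms attend 3 sessions a week for 8 weeks (24 sessions), while controls receive routine care and magazines. The article gives no dropout figures by arm, however.

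**Working it through.** **1. The plan's own figures.** 60 + 12 = 72 and 72/3 = 24 per group, as stated. The allowance is 12/72 = 16.7% of those randomised. I take 60 evaluable participants as given here. Whether 20 per group follows from f = 0.35 at 80% power is a separate question.

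**2. The visit wording side by side.**

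| Place | Eight weeks counted by |
|---|---|
| Procedures | intervention |
| Measurement, blood values | programme |
| Measurement, spirometry | study |
| Abstract, Methods | study |

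Two of the four tie the visit to treatment and two to calendar time. None says what happens to someone who stops exercising.

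**3. Cost of coupling pain to the blood values.** Input: 60 attendees. Assumption: each failure has probability p = 2% to 5%; the article gives no figure.

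- Pain alone: 60(1 − p) = 58.8 to 57.0.
- Two failure events, pain and a shared blood sample: 60(1 − p)² = 57.6 to 54.2.
- Pain scores lost from the between-group test: 58.8 − 57.6 = 1.2, up to 57.0 − 54.2 = 2.8.

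The shared-failure case is the more realistic one, because Measurement describes a blood sample taken by pinprick and the likely causes (not fasting, failed sample) affect several values together. With three independently failing variables, 60(1 − p)³ = 56.5 to 51.4.

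**4. Possible bias without baseline adjustment.** Assumptions, none from the article:

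- no true effect and 24 per arm;
- all 12 losses in the exercise arms (6 of 24, or 25%, in each) and none in control;
- dropout odds rising 2-fold to 3-fold per SD of baseline score;
- baseline to week-8 correlation r of 0.5 to 0.7.

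Simulated results:

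| r | Bias toward exercise, unadjusted | Rejection rate at nominal 5% |
|---|---|---|
| 0.5 | 0.08 to 0.12 SD | about 6% |
| 0.7 | 0.11 to 0.16 SD | about 6% to 8% |

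- Adjusted for baseline, the bias is below 0.005 SD.
- If the same total loss is spread equally (one sixth per arm) with the same dropout mechanism in every arm, the unadjusted bias is zero within simulation error and rejection is 5%.
- Extreme case: the highest-scoring 25% leave both exercise arms. The baseline mean of those who stay shifts by −φ(0.674)/0.75 = −0.42 SD. At r = 0.5 the week-8 shift is 0.5 × (−0.42) = −0.21 SD.

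**5. Scale.** With the two exercise arms equal, f = d√2/3, so f = 0.35 gives d = 0.35 × 3/√2 = 0.74 SD. A bias of 0.1 SD is about one seventh of that.

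**6. Gain from adjustment regardless of dropout.** Residual variance falls by the factor 1 − r²: 0.75 at r = 0.5 and 0.51 at r = 0.7.

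**The case against.** **It is only an unstated missing-data policy.** A condensed article may leave the analysis set and any imputation rule to the full protocol or SAP, and this one neither prescribes complete cases nor rules out imputation. That stands, and the absence of such rules is no part of this point. What remains is what the article states: a test with no baseline term, and conflicting visit wording.

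**The visit is just a time point.** A reader might infer that follow-up depends on finishing the intervention. The documents do not support that. The sentence in Procedures also covers controls, who have no exercise to finish, and two other places use study time. Only the inconsistency can be asserted.

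**The 12 are an allowance.** A reader might also infer that the authors expect 17% to drop out and intend a completers' analysis. Adding participants for attrition is ordinary inflation and is compatible with any analysis set.

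**The losses are small.** A six-variable model with independent failures at 5% would leave 60 × 0.95⁶ = 44 complete records. That requires taking every lipid fraction as a separate outcome and ignoring the shared sample. It should not be used as the expected size.

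**The bias is a chosen scenario.** Correct: 24 per group against 20 implies an allowance of four per arm, and no differential dropout is documented. Because the simulated dropout depends only on baseline, it is also no surprise that adjusting for baseline removes the bias. Dropout driven by unrecorded events after baseline would not be cured this way.

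**Change scores might be meant.** The article does not say whether week-8 values or changes enter the MANOVA. Changes would not remove the bias: a baseline shift s gives a change shift of (r − 1)s, which at r = 0.5 is as large as the week-8 shift and opposite in sign.

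**Conclusion.** The point holds in a limited form. The arm comparison for pain, glucose and cholesterol is specified without the baseline values the trial collects. Read naturally as one model, it makes the pain comparison depend on the blood sample, and the one follow-up visit is timed in conflicting ways.

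The sizes are modest. The coupling would probably cost about 1 to 3 pain scores, assuming 2% to 5% failures and a shared blood sample. Bias is zero if dropout works alike in all arms. It is roughly 0.1 SD (0.08 to 0.16) if all 12 allowed losses fall in the exercise arms and relate to baseline.

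Two limits apply. The one-joint-model reading is natural but not spelled out. The coupling also leaves untouched the within-group paired t tests and all quality-of-life and depression tests. The change is still worth making, because it uses data already collected and costs almost nothing.

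**What to change.** **(a) Visit.** In Procedures, Measurement and the Abstract, use one wording for the second assessment: 8 weeks after randomisation, for every randomised participant, whether or not the exercise programme was completed.

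**(b) Analysis.** In Data Analysis (and the Abstract), replace the joint 1-way MANOVA with a separate model for each of its outcomes, by randomised arm and adjusted for that outcome's baseline value (ANCOVA or an equivalent mixed model), followed by the pairwise arm comparisons.

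The gain comes from baseline adjustment and from separating the outcomes. With only one post-baseline value, participants who have a baseline but no week-8 value add no information on the arm contrast, so a mixed model should not be presented as recovering all 72. Getting week-8 values from participants who stop exercising is the job of (a).

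**Cost.** Wording only, with no new measurements or patients. The plan loses its single omnibus MANOVA test, and staff spend some effort bringing back participants who stop exercising.

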### Randomization and Blinding

Randomization will be conducted using a computer-generated random allocation sequence schedule conducted by a physiotherapist who is not involved in the research and has experience in research, who will randomly allocate recruited participants into the rebound exercise group, circuit training group, and the control group. To eliminate bias, the assessment of outcome will be performed by experienced assessors who will be blinded to the type of intervention as well as the intervention groups of the participants. Participants will also be instructed not to disclose their individual intervention groups to the assessors. Figure 1 shows the flow diagram.

### Procedures

Assessment of participants will be conducted at 2 stages: at baseline and at the end of 8 weeks of intervention. To ensure a comprehensive assessment, a battery of measures was chosen covering the WHO-ICF model [30]. Certain tools were selected to cover the 3 key domains proposed by the ICF: body structures and function (hematological variables, MSKP, and respiratory parameters), activity, and participation (QoL and depression). At baseline, participants will be assessed for sociodemographic characteristics, which will include personal demographic information and diabetes-specific information. The personal demographic information will include age, sex, height, weight, marital status, educational qualification, and employment. The diabetes-specific information will include type of diabetes and duration since diagnosis. At the baseline, the outcome measures to be used for these assessments are presented in the measurement section. Table 1 shows the instruments.

### Data Management

Data from the trial will be monitored by regularly scrutinizing data files for omissions and errors. All manually entered data will be double entered, and the source of any inconsistencies will be explored and resolved. Electronic data will be stored on password-protected servers at the Department of Physiotherapy, School of Health Sciences, University of KwaZulu-Natal, Durban, and written forms and data will be stored in locked filing cabinets at the Department of Physiotherapy, School of Health Sciences, University of KwaZulu-Natal, Durban. Data will only be accessible to the researcher. Each participant in the study will be provided with an identification number. All recorded data will be coded using this number.

**Figure 1 figure1:**
[figure not shown]
CONSORT flow chart.

**Table 1 table1:** Study assessment tools.

Scales or tools	Function or applications
Metronome	To provide signals for participants during exercises
Mini trampoline	For rebound exercise
Treadmill	For aerobic component of circuit training
Biodata form	To record the sociodemographic variables of participants
Alternate visual analog scale	To assess change in pain scores of participants
Beck Depression Inventory	To assess change in depression of participants
General health survey short form (SF-36)	To assess change in quality of life of participants
Accutrend plus	To assess the fasting glucose-level change and cholesterol-level change in participants
Spiro232	The spirometer will be used to measure change in forced expiratory volume, forced vital capacity, peak expiratory flow rate, and maximal voluntary ventilation

### Data Analysis

Preliminary analysis will be performed to test the normality of the data using the Kolmogorov V-Smirnov test before the analysis. Demographic data will be analyzed using descriptive statistics, whereas data on QoL and depression will be analyzed within the group using the Wilcoxon signed rank test and between the groups using the Kruskal-Wallis test. Post hoc test will be used for any significant F values.

The paired *t* test will be used within the group for pain scores, fasting glucose, and cholesterol level of the participants and between groups using 1-way multivariate analysis of variance. Post hoc test will be used for any significant F values. The level of significance will be set at .05. The SPSS version 23 will be used for the analysis.

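### The between-group tests make no adjustment for the baseline value of each outcome and do not say whether the week-8 value or the change is compared, so they give up precision

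*Protocol article*

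**What the plan says.** The protocol article's Procedures section sets two assessments: "Assessment of participants will be conducted at 2 stages: at baseline and at the end of 8 weeks of intervention". The Data Analysis section then names the between-group tests. Pain scores, fasting glucose and cholesterol are compared "between groups using 1-way multivariate analysis of variance". Quality of life and depression are compared "between the groups using the Kruskal-Wallis test". Significant results are followed by an unspecified post hoc test.

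A one-way MANOVA has group as its only factor, and Kruskal-Wallis cannot take a covariate. No ANCOVA, MANCOVA or repeated-measures model appears. The only tests that explicitly use baseline are the paired t and Wilcoxon tests within each group, which do not compare arms. The section does not state whether the between-group response is the week-8 value or the change. Table 1 describes the outcome instruments as tools for assessing change, but does not define an analysis variable. The Data Analysis section assigns no test to the respiratory outcomes, so this point concerns pain, glucose, cholesterol, quality of life and depression.

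**The concern.** The fourth objective, comparing circuit training, rebound exercise and routine care, is the one that randomisation protects, and the Results section expects it to show which exercise works best. The comparison is planned with about 20 evaluable participants per arm. At that size, chance differences in baseline are large relative to the effects sought, and no stratification on baseline values is described. If the week-8 values are compared without adjustment, part of any baseline gap passes into the estimated effect, and outcome variance that baseline could explain stays in the error term. The trial has no precision to spare, because its own sample-size inputs do not give the power claimed.

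**Working it through.** **Inputs from the protocol (Sample Size and Power Calculation).** The significance level: "The sample size (N) will be determined using Cohen table [29] at alpha=.05". Numerator degrees of freedom are k−1, "where k is the number of groups"; with three groups this is 2. The effect is given as "with effect size f=0.35". The target is "power (w) 80%, sample size n=20" per group. Attrition: "Sample size (N) will be 60, and 12 extra participants will be added to make room for attrition", which makes 72, or 24 per group.

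**Assumptions.** The baseline to week-8 correlation r is not in the protocol, so a range of 0.3 to 0.7 is shown. The value f=0.35 is taken to be on the week-8 scale. The SD is taken to be the same at both times.

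**Step 1: the plan's own figure.** Power of a one-way F test comes from the noncentral F distribution with df 2 and N−3 and noncentrality N·f². At n=20 the noncentrality is 60 × 0.35² = 7.35 and power is 65%. At n=24 it is 72 × 0.35² = 8.82 and power is 74%. Power of 80% needs 28 per group (84 in total). The stated n=20 at 80% power is therefore not reproduced; it would need f of about 0.41.

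**Step 2: baseline as a covariate.** Residual variance is multiplied by 1−r², so f becomes f/√(1−r²), and one error degree of freedom is lost. Example at r=0.5: 0.35/√0.75 = 0.404, noncentrality 7.35/0.75 = 9.8, power 78%.

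**Step 3: change scores.** The variance of a change is 2(1−r) times that of a single measurement, so f becomes f/√(2(1−r)). At r=0.5 the factor is 1 and nothing is gained. Below 0.5, change scores do worse than the unadjusted week-8 value. Relative to ANCOVA the variance ratio is 2(1−r)/(1−r²) = 2/(1+r), which exceeds 1 for every r below 1.

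| r | ANCOVA, n=20 | Change score, n=20 | ANCOVA, n=24 | ANCOVA, n per group for 80% |
|---|---|---|---|---|
| 0.3 | 70% | 50% | 78% | 25 |
| 0.4 | 73% | 57% | 82% | 24 |
| 0.5 | 78% | 65% | 86% | 21 |
| 0.6 | 85% | 76% | 91% | 18 |
| 0.7 | 92% | 87% | 96% | 15 |

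The unadjusted week-8 comparison gives 65% at n=20, 74% at n=24, and needs 28 per group. ANCOVA at n=20 reaches 80% from about r=0.53.

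**Step 4: chance imbalance.** The standard error of a baseline difference between two arms is √(2/n) SD: √(2/20) = 0.32 SD, or √(2/24) = 0.29 SD. A gap above 0.5 SD between a given pair of arms then has a chance of about 11% or 8% per outcome. Given a baseline gap b, the expected shift in the unadjusted week-8 difference is r·b; for b=0.5 SD and r=0.5 this is 0.25 SD. A change score shifts by (r−1)·b, here −0.25 SD, which over-corrects.

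**The case against.** The strongest reply is that baseline may be used after all. Table 1 speaks of change for the outcome instruments, and a one-way MANOVA or Kruskal-Wallis test on change scores is compatible with the Data Analysis section. A reader might infer from the named tests that baseline enters no between-group comparison; the text does not establish this. What stands is narrower: the response is undefined, and under either reading baseline is not adjusted for as a covariate. If change is analysed, the gain is smaller at high correlation: at r=0.7 and n=20, from 87% to 92% rather than from 65% to 92%.

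A reader might also take the missing adjustment to make the tests biased or invalid. It does not. Under randomisation the unadjusted tests keep their type I error, which already allows for chance imbalance. The shift in Step 4 is conditional on the imbalance that happens to occur.

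Three limits on the size also stand. Entry requires musculoskeletal symptoms and a BDI score of at least 11; such a restriction of range tends to lower r for pain and depression, so the lower rows of correlation matter. The value f=0.35 comes from an earlier study that is not at hand; if it was derived from change or adjusted scores, Step 2 counts the gain twice. The powers are for a single-outcome F test; joint MANOVA power cannot be computed without the correlations between outcomes.

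It can also be said that covariates are often left to an analysis plan. Here, however, the article names specific tests, and one of them cannot accept a covariate.

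**Conclusion.** The point holds as a matter of efficiency and of an undefined response variable, and it should be fixed. It is not a threat to validity. With f=0.35 assumed to be on the week-8 scale and r assumed between 0.3 and 0.7, baseline adjustment lifts single-outcome power at 20 per group from 65% to between 70% and 92%, and it beats change scores throughout that range.

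A reader might conclude that adjustment restores the 80% power the protocol claims. The documents do not support that. They give no correlation, and at r=0.5 or below adjusted power at n=20 stays under 80%. Adjustment does not replace correcting the sample-size statement.

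**What to change.** State the response and the adjustment explicitly: analyse the week-8 value on randomised group plus the baseline value of the same outcome. If change is preferred for presentation, keep baseline as a covariate; the estimated group difference is then the same.

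- **Pain, glucose, cholesterol:** use MANCOVA with the baseline values if the joint test is kept, so that adjustment does not mean dropping it. Follow with ANCOVA for each outcome, reporting adjusted differences with 95% confidence intervals for each exercise arm against control and for rebound against circuit. Name a multiplicity-adjusted post hoc procedure for these pairs.
- **BDI and SF-36, where skewed:** replace Kruskal-Wallis by rank ANCOVA with baseline, or by a proportional-odds model with baseline.

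The change should be made before any between-group result is seen. It needs no new data, visits or participants, and the SPSS version already named can be used. It costs one error degree of freedom per univariate model, and one per baseline covariate in the joint model. The sample-size paragraph should be corrected separately.

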### Objective

The objective of this research is to investigate the effect of rebound exercises and circuit training and compare them to the routine care of type 2 diabetic patients. The objectives of this research are as follows;

To investigate the effect of rebound exercises on glycemic control, cholesterol level, respiratory parameters, pain scores, depression, and QoL among type 2 diabetes patientsTo investigate the effect of CRT on glycemic control, cholesterol level, respiratory parameters, pain scores, depression, and QoL among type 2 diabetes patientsTo investigate the effect of routine care (control group) on glycemic control, cholesterol level, respiratory parameters, pain scores, depression, and QoL among type 2 diabetes patientsTo compare the effect of circuit training, rebound exercises, and routine care on glycemic control, cholesterol level, respiratory parameters, pain scores, depression, and QoL among type 2 diabetes patients.

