### Measurement

The following measurement would be taken during the data collection they are as follows:

Sociodemographic variables: The sociodemographic variables of the participants will be recorded before the commencement of the study. These include age, race, gender, height, weight, educational level, duration of diabetes, level of pain, blood pressure, pulse rate, and heart rate.Pain intensity: The alternate visual analog scale will be used to assess the pain level of the participants. The participants will be requested to rate on a 0-10 scale, the level of pain they felt 6 weeks before and at present. On the scale, 0 indicates no pain or no interference, whereas 10 is pain as bad as it could be/extreme interference [26]. The alternate visual analogue scale has been reported to have a high validity, increased patient compliance, greater sensitivity of measurement, and reduced bias [26].BDI: This will be used to assess and screen participants for depression. The BDI is a 21-item multiple choice self-reported inventory, widely used to assess the presence and degree of depression in adolescents and adults [27]. The BDI is a self-administered questionnaire and it has a high test-retest reliability (Pearson *r*).QoL: The General Health Survey Short Form (SF-36) will be used to measure changes in the participant’s QoL. The instrument has shown good validity and reliability of Cronbach alpha of .85 and reliability coefficient of .75 for all the domains except social functioning [28]. The short form, SF-36, measures perceived health in the areas of physical functioning, role-physical, bodily pain, general health, vitality, social functioning, role-emotional, and mental health, with higher scores (range 0-100) reflecting better-perceived health.Biochemical parameters: Fasting blood glucose in mmol/L, blood total cholesterol (TC) in mmol/L, low-density lipoprotein (LDL) mmol/L, very low-density lipoproteins (VLDL) mmol/L, and high-density lipoprotein (HDL) mmol/L will be determined at baseline and after 8 weeks of the program. A blood sample will be taken by pinprick using Accu-check Sofclix Pro Roche Diabetes care, South Africa. Then, the following parameters will be evaluated: fasting glucose level using Accutrend (Roche Diagnostics, GmbH Germany); HDL-C using PEG þ cholesterol oxidase (Roche Diagnostics GmbH Germany); triglycerides using glycerol phosphate-PAP (Roche Diagnostics GmbH Germany); and TC using cholesterol oxidase-PAP (Roche Diagnostics GmbH Germany) to evaluate TC, LDL, VLDL, and HDL-C.Pulmonary parameters: Pulmonary function parameters will be measured at baseline and after the 8 weeks of the study using Spiro 232 (PK Morgan, India). The following parameters will be measured: Forced expiratory volume in first second (FEV_1_) (It), forced vital capacity (FVC), FEV_1_/FVC ratio, peak expiratory flow rate, and maximal voluntary ventilation (It/min). The spirometer will be connected to a computer that will record all the values.

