## Results

The results of this study are expected to provide additional information on the effect of rebound exercise and circuit training in the management of patients with musculoskeletal complications of diabetes in South Africa. It is hoped that it will lead to improvement in the QoL, reduction in MSKP and depression, improvement in glycemic control, reduction in cholesterol level, as well as improvement in respiratory capacity of type 2 diabetes patients. It is also expected to give information about which of the exercises is most effective in the management of patients with musculoskeletal diabetes complications in terms of pain relief, glycemic control, cholesterol level, improvement in QoL, level of depression, and respiratory capacity.

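### The protocol article names no primary outcome and applies one unadjusted .05 to several outcome families, so the chance of a false-positive between-group result is about 13% to 40%, not 5%

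*Protocol article*

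**What the plan says.** The Objective section gives four aims, one for each arm and one comparing the three arms. Each repeats the same list: "glycemic control, cholesterol level, respiratory parameters, pain scores, depression, and QoL among type 2 diabetes patients". No outcome is called primary there, in the abstract or in the Results section.

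The Measurement section turns the list into instruments. For pain, "The alternate visual analog scale will be used to assess the pain level of the participants". Of the Beck Depression Inventory (BDI) it says "This will be used to assess and screen participants for depression". It also lists the SF-36 with eight areas, fasting glucose, four cholesterol fractions and five spirometry values.

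The Sample Size section uses a table lookup "where k is the number of groups, with effect size f=0.35". It cites a previous study and 80% power, arrives at 20 per group, and does not say which outcome the effect size describes.

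The Data Analysis section assigns these tests:
- **Quality of life and depression:** Wilcoxon signed rank within group, Kruskal-Wallis between groups.
- **Pain, fasting glucose and cholesterol:** paired t test within group, one-way MANOVA between groups.
- **After either between-group analysis:** "Post hoc test will be used for any significant F values".
- **Throughout:** "The level of significance will be set at .05". The abstract agrees: "Alpha will be set at .05".

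The section assigns no test to the respiratory measures. The Results section says of the trial: "It is also expected to give information about which of the exercises is most effective", and names all six domains.

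**The concern.** A .05 level describes the trial's error rate only if one test decides the question. Here several families of tests each use the full .05 and no outcome is ranked above another. A significant result on any of them could be presented as the trial's answer. The stated aim of showing which exercise works best across six domains makes that more likely.

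The sample size has the same gap. Power belongs to a particular outcome and comparison, and with no outcome attached to f=0.35 the 80% cannot be read as the power for any claim the trial will make. The choice of primary outcome drives the sample size, so it belongs in the protocol rather than in an analysis plan.

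**Working it through.** **1. Between-group omnibus tests the text supports**

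| Outcome | Test (Data Analysis) | Number of tests |
|---|---|---|
| Pain, glucose, cholesterol | one joint MANOVA | 1 |
| BDI | Kruskal-Wallis | 1 |
| Quality of life | Kruskal-Wallis | 1 (single score) or 8 (SF-36 domains) |
| Respiratory measures | none assigned | 0 |

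The total is 3 or 10. The article does not say how quality of life is scored for testing, so both readings are carried.

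**2. Chance of at least one false positive when nothing has an effect**

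For m independent tests at .05 the chance is 1 − 0.95^m:
- m = 1: 0.050, the stated level.
- m = 3: 1 − 0.95^3 = 0.143.
- m = 10: 1 − 0.95^10 = 0.401.

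The outcomes are probably correlated, but the article gives no correlations, so the values below are assumptions. Simulated F tests with 20 per group and a common correlation give:

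| Assumed correlation | 3 tests | 10 tests |
|---|---|---|
| 0 | 14% | 40% |
| 0.3 | 14% | 36% |
| 0.5 | 13% | 29-30% |
| 0.7 | 11% | 22% |

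**3. Within-arm tests**

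The outcomes with an assigned within-arm test are pain 1, BDI 1, SF-36 domains 8, glucose 1 and cholesterol fractions 4, which makes 15. Over three arms that is 15 × 3 = 45 tests. Expected false positives are 45 × 0.05 = 2.25. With one quality-of-life score the count is 8 × 3 = 24, and 24 × 0.05 = 1.2.

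**4. Protection from the MANOVA**

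If no component differs between groups, follow-up tests run only after a significant MANOVA, so their error stays at about .05. If one component truly differs, the MANOVA tends to be significant. The follow-ups on the other components are then open at .05 each, because no adjusted method is named.

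**5. What the sample size can support**

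The exact noncentral F for three groups, with f = 0.35 and λ = N × f², gives 65.4% power at 20 per group and 74.2% at 24. It needs 28 per group for 80% (81.2%; 27 gives 79.6%). The stated 20 per group is therefore not reproduced. That is a separate matter, but it bears on the power that would have to be restated.

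Keeping all outcomes co-equal is not affordable. Bonferroni over 10 tests (.005 each) leaves 31% power at 20 per group.

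For two contrasts against control at .025 (the first Holm step), the standardized difference implied by f depends on how the means are spread. Taking 2f = 0.70 to f√6 = 0.857, each contrast has about 46-65% power at 20 per group and 55-74% at 24.

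**The case against.** **A fuller document may settle it.** The analysis plan and registry record are not shown, and either may name a primary outcome or a post hoc method. That stands for the post hoc method, whose absence alone would be no finding. It does not remove the point about the decision rule: the article itself states a single .05 over several families and a sample size tied to no outcome.

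**The inflation could be modest.** If quality of life is one score, the between-group figure is about 13-14%. That stands, and it is why the result is given as a range.

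**The reference to a significant F after Kruskal-Wallis is a wording slip.** Kruskal-Wallis gives no F, but a significant omnibus result is plainly meant. Read literally, the sentence would allow fewer follow-up tests, not more. This needs tidying and does not itself inflate error.

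**Stronger readings a reader might infer.** The instruments yield about 20 measures, which suggests 20 separate tests at .05 and a 64% error (1 − 0.95^20). The between-group plan does not say that: pain, glucose and cholesterol share one MANOVA. Adding five spirometry comparisons to reach 15 tests (54%), or counting 60 within-arm tests, also goes beyond the text. No test is assigned to spirometry in the Data Analysis section, and the abstract's general mention of MANOVA suggests a joint test if anything. Nor is it right that the MANOVA gives no protection; it does when no component changes.

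**Conclusion.** The point holds. On the article's own text there is no primary outcome, the effect size belongs to no outcome, and one unadjusted .05 covers several outcome families. Between groups, the chance of at least one false positive with no effect anywhere is about 13-14% for 3 tests and 40% for 10 independent tests. With 10 tests it falls to about 29-30% or 22% at assumed correlations of 0.5 or 0.7. Even 3 tests at correlation 0.7 give about twice the stated level. The within-arm tests add up to about 2.25 expected false positives.

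These figures rest on how quality of life is scored, on the assumed correlations, and on treating the MANOVA as one test. They do not include follow-up comparisons when some components truly change, where the MANOVA no longer protects the rest.

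The documents do not settle which outcome should be primary. Pain comes first in the abstract's objective and is an inclusion requirement, but the Objective section puts glycemic control first. The Theoretical Framework cites the sample-size source for quality of life and says the effect of rebound exercise on musculoskeletal pain is undocumented. So f=0.35 cannot simply be assigned to pain.

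**What to change.** Before any outcome data are seen:
1. Name one primary outcome. Pain is a candidate, but the choice is the sponsor's.
2. State which outcome f=0.35 refers to. If it is not the primary, give an effect assumption for the primary. Restate the power for the planned comparisons.
3. For the primary outcome, compare each exercise arm with control at a family-wise .05, for example with Holm over the two contrasts. Replace the rule about significant F values by these contrasts.
4. Label every other outcome secondary or exploratory, with 95% confidence intervals and adjusted p-values. State whether quality of life is one score or eight domains.
5. Report within-arm changes descriptively, without significance claims.
6. Align the registry record if it does not already agree.

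Most of this is wording. There are two real costs. Secondary outcomes can no longer carry a stand-alone efficacy claim. The restated power may be below 80%, in which case the sponsor must accept that or recruit more participants.
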